### One year follow-up

Statistically, it is assumed that some of the participants in the study will develop arm lymphedema. Furthermore, previous studies have found a highly variable response to resistance exercise [10, 22]. A one year exploratory, hypothesis generating follow-up has been planned as it provides an opportunity to determine how many participants develop arm lymphedema and whether individual variability in response to the resistance exercise sessions is related to subsequent lymphedema incidence. Measurements will include 1RM strength in the four resistance exercises, DXA, BIS and symptom severity (VAS) as described, and a structured interview by the first author to determine other known and theoretical risk factors.

### Blinding

All data collection and analysis will be conducted by study personnel with no knowledge of group (low- / high-load first) allocation.

### Sample size and analytical plan

The sample size calculation is based on changes in L-Dex scores between baseline and 72 h post-resistance exercise sessions. From results of Cormie et al. [10] we hypothesize the standard deviation in the distribution to be 1.9 units. No published normative change scores exist for the at-risk population, as well as no evidence regarding a threshold for a clinically significant acute change. For patients with BCRL a change score of 2L-Dex units is considered clinically relevant based on clinical experience. We believe that an L-Dex of 2 units is too conservative in the at-risk population, and have therefore set a threshold at 3L-Dex units. Thus, if there is no difference between groups, then 18 patients are required to be 90 % sure that the limits of a two-sided 90 % confidence interval will exclude a difference in means of more than 3.0. To allow for possible drop-outs we plan to include 20 patients.

Data will be analyzed using the Statistical Package for Social Sciences (SPSS) software (version 19) for Windows (IBM SPSS, Chicago, IL). Analysis will include standard descriptive statistics and both intention to treat and per-protocol analysis will be performed. Using a generalized estimating equations framework for continuous outcomes to determine time (baseline, pre-, post, 24- and 72 h) and intervention (low-/ heavy-load) effects, the interaction between time and intervention will be considered [23]. Two-tailed *p* < 0.05 will be taken as evidence of statistical significance.

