## Design

This study is a randomized, cross-over trial (Table 1 here).

**Table 1 Tab1:** Trial registration data

Trial registration data	
Primary registry and trial identify number	Current Controlled Trials ISRCTN97332727.
Date of registration in primary registry	12 February 2015.
Secondary identifying numbers	H-3-2014-147, 30-1430
Source of monetary or material support	University Hospitals Centre for Health Research, Copenhagen University Hospital Rigshospitalet
Primary sponsor	University Hospitals Centre for Health Research, Copenhagen University Hospital Rigshospitalet
Secondary sponsor	
Contact for public queries	KB, MHS, PhD-stud. [contact], [name], [name]
Contract for scientific queries	KB, MHS, PhD-stud. [contact], [name], [name]
Public title	A trial to detect differences in arm volume after low- and heavy-load resistance exercise among patients receiving adjuvant chemotherapy for breast cancer at risk for arm lymphedema: Study Protocol
Scientific title	A randomized cross-over trial to detect differences in arm volume after low- and heavy-load resistance exercise among patients receiving adjuvant chemotherapy for breast cancer at risk for arm lymphedema: Study Protocol
Countries of recruitment	Denmark
Health condition or problem studied	Breast cancer-related arm lymphedema
Intervention	Heavy vs low load resistance exercise for the upper extremities
Key inclusion and exclusion criteria	Inclusion criteria: > 18 years of age, unilateral breast surgery, axillary node dissection, undergoing adjuvant chemotherapy for breast cancer
	Exclusion criteria: Previously treated for breast cancer, diagnosis of BCRL and/or currently receiving treatment for BCRL, or having conditions hampering resistance exercise of the upper body, or having participated in regular upper-body heavy resistance exercise during the last month
Study type	Interventional
	Randomized cross-over, assessor blinded
	Safety
Date of first enrolment	31-03-2015
Target sample size	40
Recruitment status	Recruiting
Primary outcome	Arm extracellular fluid (L-dex score) post-, 24- and 72 h post exercise
Key secondary outcomes	Arm volume (ml) post-, 24- and 72 h post exercise

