### Concealed randomization

Prior to the study, a computer-generated random sequence will be generated by an external researcher not otherwise affiliated with the study, and concealed in opaque envelopes. Group assignment will be disclosed to the first author by telephone after study inclusion and participation in the familiarization period. Participants will be allocated using a 1:1 ratio to partake in either low- or heavy-load resistance exercise first.

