DXA is another measurement method that can differentiate between tissue types giving an estimate of BMC, fat mass and lean mass where the lean mass component includes extracellular fluid [20, 21, 40]. DXA has been found to be sensitive to changes in tissue composition, making it an ideal measurement method to monitor BCRL over time as fluid components are replaced with adipose tissue. Furthermore, DXA allows for analysis of separate regions of the arm, of potential clinical importance for patients where swelling is confined to a specific region of the arm or hand [20, 21, 40, 41]. In this study we scan the arms separately and use software with a high resolution allowing for more precise definition of ROIs and the possibility to define bone and soft tissue manually as described by Gjorup et al., with a low inter-rater variation (ICC ≥,9990) [20]. To the authors’ knowledge, this is the first time that DXA, with this software, will be used to detect volume changes in the BCRL at-risk population adding new insights into the application of this measurement method.

This exploratory study utilizes a cross-over design to determine acute changes in extracellular fluid and arm volume. This design lends more statistical power, with the practical advantage of a smaller sample size, as between-patient variation is inherently eliminated [42], providing a framework for an efficient comparison between the two resistance exercise loads. However, this study can only provide us with information regarding extracellular fluid and arm volume changes after one resistance exercise session, limiting the generalizability to repeated resistance exercise training and long-term effects on arm volume. Nonetheless, this study can lend initial evidence regarding the safety of heavy-load lifting and can help guide future studies and optimal exercise prescription.

Finally, women at risk for BCRL still receive risk reduction advice including avoiding heavy lifting [43, 44]. This advice can lead to women being apprehensive about lifting heavy loads with consequences for daily living (e.g., not lifting children, groceries, etc.). However, this advice is not based on research and knowledge gained from this study can provide a preliminary evidence base for guiding risk reduction practices involving intermittent heavy-load activity necessary for daily living.

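### The 18-patient sample size is a two-parallel-group total applied to a cross-over; it overstates the number needed, and the stated 90% power is not this design's power

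*Protocol article*

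**What the plan says.** The Design section states: "This study is a randomized, cross-over trial". Randomization is to order only: "Participants will be allocated using a 1:1 ratio to partake in either low- or heavy-load resistance exercise first". Each woman therefore supplies a result under both loads.

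The section Sample size and analytical plan gives these inputs:

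- Endpoint: "The sample size calculation is based on changes in L-Dex scores between baseline and 72 h post-resistance exercise sessions".
- Spread: "we hypothesize the standard deviation in the distribution to be 1.9 units", taken from a cited study of women who already had arm lymphedema (BCRL).
- Margin: the authors "have therefore set a threshold at 3L-Dex units". They explain: "We believe that an L-Dex of 2 units is too conservative in the at-risk population". The 2-unit figure is attributed to clinical experience in patients with BCRL. The same paragraph says that no evidence exists for a threshold in the at-risk population.
- Result: "if there is no difference between groups, then 18 patients are required", for 90% assurance with a two-sided 90% confidence interval, raised to 20 for drop-outs.

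The Discussion credits the design with more power, "with the practical advantage of a smaller sample size, as between-patient variation is inherently eliminated". Table 1 gives a target sample size of 40, against 20 in the Abstract, the recruitment section and the sample size section.

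**The concern.** The calculation speaks of a difference between groups, but the trial has no parallel treatment groups. The relevant variance is that of each woman's heavy-minus-low difference, and all completers contribute to it. The paragraph does not say whether 1.9 is the SD of a single-session change or of that within-person difference, and it gives no correlation between the two sessions. If 18 comes from a formula for independent groups, the printed number and the printed power both describe another design, and the efficiency claimed in the Discussion was never used in sizing the trial.

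At stake is whether a reader can tell what precision this trial will have, and so how narrow a difference it could exclude.

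**Working it through.** **Inputs from the protocol article:** SD 1.9; margin 3.0; two-sided 90% interval (two one-sided tests at 5%, z = 1.645); 90% power with true difference 0 (each tail 5%, z = 1.645); 18 patients, 20 with drop-outs.

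**Assumption:** the correlation ρ between a woman's two session changes is not given, so a range is shown.

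**Step 1. Reproduce 18.** Two independent groups:

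n per group = 2 × 1.9² × (1.645 + 1.645)² / 3² = 2 × 3.61 × 10.82 / 9 = 8.68, so 9 per group and **18 in total**.

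This is the stated figure. Close variants miss it: without halving the type II error the total is 14, and with a 95% interval it is 22.

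**Step 2. Can a cross-over reading give 18?** For the paired contrast:

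n total = SDd² × (1.645 + 1.645)² / 3², with SDd = 1.9 × √(2(1 − ρ)).

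- If 1.9 is the single-session SD and ρ = 0: SDd = 2.69, n = 8.68, so 9 patients.
- If 1.9 is already the SD of the within-person difference (the same as ρ = 0.5): n = 4.34, so 5 patients.
- To need 18: SDd = 3 × √18 / 3.29 = 3.87. With a single-session SD of 1.9 this implies ρ = 1 − 3.87² / (2 × 3.61) = −1.07, which is impossible.

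No cross-over reading of 1.9 leads to 18.

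**Step 3. Size and power for the actual design at margin 3.** Two one-sided t-tests, df = n − 2:

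| ρ | SDd | Completers for 90% power | Power with 18 | Power with 20 |
|---|---|---|---|---|
| −0.25 | 3.00 | 13 | 98.4% | 99.2% |
| 0 | 2.69 | 11 | 99.6% | 99.8% |
| 0.25 | 2.33 | 9 | above 99.9% | above 99.9% |
| 0.5 | 1.90 | 7 | about 100% | about 100% |

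**Step 4. What the same patients give against ±2** (same method):

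| SD | ρ | Power with 18 | Power with 20 |
|---|---|---|---|
| 1.9 | −0.25 | 71% | 78% |
| 1.9 | 0 | 83% | 88% |
| 1.9 | 0.25 | 93% | 96% |
| 1.9 | 0.5 | 99% | above 99% |
| 2.5 (assumption) | 0 | 49% | 57% |
| 2.5 (assumption) | 0.3 | 73% | 79% |

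At ±3 with SD 2.5, power stays at about 93% (18) and 95% (20) at ρ = 0.

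**Step 5. The 40 in Table 1.** The two-group formula at margin 2 gives 2 × 3.61 × 10.82 / 4 = 19.53, so 20 per group and 40 in total. The match is an observation; the protocol does not say where 40 comes from.

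**The case against.** The strongest reply is that nothing is endangered. The error makes the trial larger than its stated aim requires, the study calls itself exploratory, and 20 women remain more than enough at margin 3. That stands, and it limits the point to correcting a misdescribed calculation. It does not rescue the sentence, which states a requirement and a power that no cross-over reading of the inputs gives.

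A reader might go further and infer that the margin was wrongly widened to 3, since 20 cross-over patients already support 2 and the wider margin gains nothing. The document does not support this, for four reasons:

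- The reason given for 3 is clinical belief, not feasibility. The 2-unit figure belongs to women with BCRL, whom this trial excludes, and the absence of an evidence-based threshold is disclosed.
- A margin is set by what matters clinically, not by what the sample can afford.
- At margin 3 with 18 completers, a true difference of 2 would be declared equivalent in 45% (ρ = 0) to 69% (ρ = 0.5) of trials. Under that margin this is a correct verdict. It counts as harm only if 2 has already been accepted as the limit.
- Support for ±2 is conditional. At ρ = 0 the t-based power is below 90% with either 18 or 20 completers, and it falls further if the correlation is negative or the SD exceeds 1.9. The SD is borrowed from a different population, so the wider margin does give protection against a misjudged SD.

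**Conclusion.** The statement that 18 patients are required for 90% power is wrong for this trial. The number is the two-parallel-group total of 9 + 9. For the cross-over contrast at margin 3, the requirement is about 11 completers at correlation 0 and about 7 at 0.5, and 18 completers give at least 99.6% power at correlation 0 or above (98.4% at −0.25). The error is conservative.

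These figures take 1.9 as the single-session SD. If it is already the SD of the within-person difference, the row for 0.5 applies. They also assume a normally distributed contrast and a true difference of zero, as the protocol does.

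The 3-unit margin is not shown to be an error. What follows is narrower: the design is more precise than the paragraph suggests, so the result can usefully be read against 2 units as well.

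**What to change.** 1. Recompute the sample size for the within-person heavy-minus-low difference in L-Dex change to 72 hours.
2. State whether 1.9 is the SD of a single-session change or of that difference. If the former, give an assumed correlation range.
3. Replace the sentence on 18 patients with the power of the cross-over contrast for 18 to 20 completers. Keep enrolment at 20.
4. Reconcile the 20 with the target of 40 in Table 1.
5. Keep ±3 as the margin with its stated rationale, and pre-specify that the 90% confidence interval is also reported against ±2, so that a result inside 3 but not inside 2 is visible as such.

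The cost is one rewritten paragraph and one table entry, with no additional patients. The downside lies in item 5: at ±2 the power is only 83% (18 completers) to 88% (20) at correlation 0, 71% to 78% at −0.25, and 49% to 57% at correlation 0 if the SD were 2.5. Failure to exclude 2 units should therefore not be read as evidence of a difference, and the paragraph should say so.

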### Outcomes (pre- and post, 24- and 72-hours after resistance exercise)

Measurements will be performed by medical technicians with no knowledge of group (low- / high-load first) allocation at the Department of Clinical Physiology and Nuclear Medicine at the Copenhagen University Hospital, Rigshospitalet. Participants are advised to maintain their normal activities during study participation. At all assessment points, participants will be asked about their physical activities, and any extraordinary activities will be recorded.

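### GEE at p<0.05 with only 18 to 20 women: if run with uncorrected robust variance and chi-square Wald tests, the time-by-load interaction has about 12-13% type I error, so small-sample t/F inference should be specified

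*Protocol article*

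**What the plan says.** All of the analysis text is in the Protocol article, section Sample size and analytical plan.

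- **Method:** the continuous outcomes are modelled "Using a generalized estimating equations framework for continuous outcomes", to estimate "time (baseline, pre-, post, 24- and 72 h) and intervention (low-/ heavy-load) effects", with the time-by-load interaction also examined.
- **Level:** "Two-tailed *p* < 0.05 will be taken as evidence of statistical significance".
- **Size:** "18 patients are required to be 90 % sure that the limits of a two-sided 90 % confidence interval will exclude a difference" of more than 3.0 L-Dex units, and "To allow for possible drop-outs we plan to include 20 patients".
- **Planning inputs:** "we hypothesize the standard deviation in the distribution to be 1.9 units", and the authors "have therefore set a threshold at 3L-Dex units".
- **Readings:** the section headed "Outcomes (pre- and post, 24- and 72-hours after resistance exercise" gives four measurement times per session. The safety section counts eight scans, which agrees with two sessions of four.

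The article does not state the working correlation, whether the variance is robust or model-based, or which reference distribution the tests use. The two-sided 90% interval appears only in the sample-size sentence.

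**The concern.** Standard GEE inference is a large-sample argument in the number of independent clusters. Here the clusters are women, not readings: 18 to 20 of them, each with eight correlated readings. The usual Wald test treats the estimated covariance of the interaction contrasts as known. With so few clusters that uncertainty matters, and it matters more as the number of contrasts tested together rises.

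The choice of method and the sample size are both fixed in the text, so the mismatch is more than an unstated detail. The study is labelled a safety study and hypothesizes no difference between loads. An interaction test that rejects too often would produce false signals that load matters. An interval that is too narrow would, to a smaller degree, favour a false conclusion that the loads are equivalent.

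**Working it through.** **The plan's own figure.** Inputs from the sample-size paragraph are SD 1.9, margin 3.0, two-sided 90% interval, 90% power and true difference 0. The two-group equivalence formula gives n per group = 2 × (1.9 × (1.645 + 1.645) / 3)² = 8.68, rounded up to 9, so 18 in total. The stated 18 is reproduced. The formula uses normal quantiles.

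**Interaction test, exact.** Assume complete balanced data, normal within-person contrasts, no period term, uncorrected robust variance and a Wald statistic W referred to chi-square. Let p be the number of contrasts and n the number of women. The robust variance divides by n, so W = T² × n/(n−1), where T² is Hotelling's statistic. Since T² × (n−p)/(p(n−1)) follows F(p, n−p),

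P(W > c) = P(F(p, n−p) > c(n−p)/(np)), where c is the 95% chi-square point on p df.

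Four readings per session give p = 3 and c = 7.815:

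| n | F threshold | Rejection rate at nominal 5% |
|---|---|---|
| 20 | 7.815 × 17/60 = 2.214 | 12.4% |
| 18 | 7.815 × 15/54 = 2.171 | 13.4% |

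A single contrast has p = 1 and c = 3.841:

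| n | F threshold | Rejection rate at nominal 5% |
|---|---|---|
| 20 | 3.841 × 19/20 = 3.649 | 7.1% |
| 18 | 3.841 × 17/18 = 3.628 | 7.4% |

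**Where the inflation comes from.** The standard errors are low by √((n−1)/n), which is 0.975 at n = 20 and 0.972 at n = 18. Removing that shrinkage but keeping chi-square changes the threshold to c(n−p)/(p(n−1)). The 3-df rates become 11.1% (n = 20) and 11.9% (n = 18). Most of the excess over 5% therefore comes from the chi-square reference. Referring T² to F(p, n−p) restores exactly 5% in this balanced case.

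**90% interval for one contrast.** The uncorrected multiplier, on the scale of the t interval, is 1.645 × √((n−1)/n).

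| n | Uncorrected multiplier | t quantile, n−1 df | Coverage | One-sided error | t interval wider by |
|---|---|---|---|---|---|
| 20 | 1.603 | 1.729 | 87.5% | 6.3% | 1.729/1.603 = 1.079, 8% |
| 18 | 1.599 | 1.740 | 87.2% | 6.4% | 1.740/1.599 = 1.088, 9% |

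**Simulation.** Each setting had 2,000 runs, with four readings per session, n = 18 or 20, independence or exchangeable working correlation, and two true covariance structures.

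- *Uncorrected robust variance:* 12-15% type I error without period-by-time terms, 13-17% with them.
- *Mancl-DeRouen corrected variance, chi-square kept:* about 8-12%. A corrected variance alone is therefore not enough.
- *Model-based variance:* 0-4% type I error, and at least 92% coverage of a nominal 90% interval.

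**If the target were 40.** Table 1 lists a target of 40, against 20 elsewhere. With 40 clusters the exact 3-df rate would still be 8.2%.

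**The case against.** The strongest reply is that the article never says the variance is robust and uncorrected. Such details are commonly left to a fuller document that is not shown, and with model-based variance the simulated test was not inflated at all. This stands, and it makes the figures conditional. It does not remove the point. In the simulated settings neither plain form held 5%: the robust form was well above, and the model-based form was below, with intervals wider than needed.

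Three stronger readings are tempting, and the documents do not support them.

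- **Type I error of 16-18%.** The analysis paragraph lists five time labels, and a 4-df interaction would give 16.0% (n = 20) or 17.6% (n = 18). That needs five readings in each session. The abstract, the outcomes section and the count of eight scans all give four, so the extra label is at most an ambiguity.
- **A materially false equivalence claim.** The article does not say that the 90% interval will come from the GEE, and the effect would be small. At n = 18, if 1.9 is the SD of the within-person difference, the half-width is 0.72 (uncorrected) against 0.78 (t-based). If 1.9 is the SD of each session's change and sessions are uncorrelated, it is 1.01 against 1.10. Gaps of 0.06 to 0.09 against a margin of 3.0 would rarely alter the conclusion. The larger inflation, in the interaction test, errs towards finding a difference.
- **Bias from withdrawal.** The safety section withdraws women with swelling or a persisting L-Dex score, so a reader might infer that GEE estimates are biased by outcome-related missingness. The documents give no rate from which to size this, and every figure above assumes complete data.

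It is also fair that GEE is a legitimate method for this design, that the article calls the study exploratory, and that it does not name the interaction as the primary test.

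**Conclusion.** The point holds in conditional form. With 18 to 20 clusters and GEE run with uncorrected robust variance and Wald chi-square tests, the 3-df interaction has about 12-13% type I error instead of 5%. A single contrast has about 7%, and a nominal 90% interval covers about 87%. These figures rest on complete balanced data, normal within-person contrasts and no period term; adding period-by-time terms raised the simulated interaction error to 13-17%.

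The documents do not support saying that the planned test has this error unconditionally, nor that standard errors that are too small are the main cause. The consequence is substantial for the multi-df interaction test and modest for the equivalence interval. It is worth correcting because methods with suitable small-sample error are available for a continuous outcome and need no extra participants.

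**What to change.** Base inference on small-sample methods and say so in the analysis text.

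1. **Primary contrast.** For each woman, take the heavy-minus-low difference in pre-to-72 h L-Dex change. Analyse it adjusted for period, with a t-based 90% interval on n−2 df, and compare that interval with the 3.0-unit margin.
2. **All time points.** Use a REML linear mixed model with Kenward-Roger degrees of freedom. Alternatively, keep GEE with a bias-corrected variance together with a t or F reference. The correction without the changed reference is not sufficient.
3. **Time levels.** State that the pre-exercise reading is the reference and that there are four times per session, so that the interaction has 3 df.

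The cost is wording only. Intervals become about 8 to 9% wider than those from uncorrected robust GEE, and n−2 in place of n−1 df hardly changes this (t quantile 1.746 against 1.740 at n = 18). The mixed model reaches its nominal level only if its covariance structure is adequate, so that structure should be fixed in advance. The software named should also be checked for the chosen option; the t-based contrast needs no special routine.

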## Methods

### Participants / Recruitment

Twenty women allocated to adjuvant chemotherapy for breast cancer consisting of three cycles of 3-weekly epirubicin followed by three cyles of 3-weekly docetaxel will be recruited from municipality lead rehabilitation centers in the Copenhagen area and from a waiting list to the *Body and Cancer* program [11, 12], at the University Hospitals Center for Health Research (UCSF) at the Copenhagen University Hospital, Rigshospitalet. All patients will be screened for inclusion by health professionals (nurse or physical therapist) at the respective centers. Potential participants fulfilling inclusion criteria; over 18 years of age, unilateral breast surgery, axillary node dissection, and initiating /undergoing adjuvant chemotherapy for breast cancer (stage I - III) will be contacted during their first three cycles of chemotherapy (Fig. 1). Patients previously treated for breast cancer, with a diagnosis of BCRL and/or currently receiving treatment for lymphedema, or having conditions hampering resistance exercise of the upper body, or having participated in regular (>1 × / week) upper-body heavy resistance exercise during the last month will be excluded.

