### Exercise sessions

Participants will engage in a familiarization period, comprising of two training sessions up to one week apart, after the third cycle of chemotherapy. Each session will start with a 10- minute aerobic warm-up using a cross-trainer (Glidex, Technogym®, Gamettola, Italy). During the first familiarization session participants will be introduced to four upper-body exercises (chest press, latissimus pull down, triceps extension (Technogym®, Gamettola, Italy) and biceps curl (free weights)) followed by a 1RM strength test in each exercise. At the second familiarization session, two sets of 10–15 RM will be performed and a new 1RM strength test will be undertaken to ensure accuracy of subsequent exercise prescription. Participants will engage in the first experimental session after the first cycle of docetaxel (fourth chemotherapy), followed by a wash-out period of 6 days. Two sets of 15–20 RM of each exercise will be performed during low-load resistance exercise and three sets of 5–8 RM during heavy-load. All sets will be performed to muscle fatigue in sessions individually supervised by the first author (a physical therapist with experience in exercise prescription for women with breast cancer) at training facilities located at Rigshospitalet.

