## Discussion

Participating in resistance exercise during adjuvant chemotherapy for breast cancer has been associated with increases in muscle strength [25–29], lean body mass [25, 28], and self-esteem [25], and has been found to mitigate fatigue and to maintain quality of life [29]. Furthermore, there is evidence to suggest that resistance exercise might be associated with a higher completion rate of planned chemotherapy [25]. Moreover, generalized edema characterized by an increase in the size of the interstitial compartment of extracellular fluid is a potential side effect to taxane-based chemotherapy [30, 31]. Thus, swelling as a consequence of increased fluid in addition to an impairment of lymph fluid transport, could potentially contribute to swelling of the at-risk arm. Hypothetically, this could be thwarted by resistance exercise due to increased lymph clearance likely through the effects of the muscle pump [32, 33], lending additional rationale for instigating resistance exercise during adjuvant chemotherapy.

To our knowledge, studies investigating the safety and efficacy of resistance exercise in patients at risk for BCRL have utilized low- to moderate-resistance exercise intensities [6, 7], with only one cross-sectional study [11] investigating heavy-load resistance exercise. Indeed, in a paper identifying the top 10 research questions related to physical activity and cancer survivorship, Courneya et al. [34] highlighted the need for studies investigating safety and optimal exercise prescription, and specifically the role of vigorous-intensity activity, as important research areas [34].

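### The stated cross-over model has time, load and their interaction but no period term, although a shift between session 1 and session 2 is plausible

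*Protocol article*

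**What the plan says.** All references are to the Protocol article.

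- **Design and allocation.** The Design section states: "This study is a randomized, cross-over trial". Concealed randomization adds: "Participants will be allocated using a 1:1 ratio to partake in either low- or heavy-load resistance exercise first". The unit of randomisation is therefore the order of the two loads.
- **Timing.** Exercise sessions: "Participants will engage in the first experimental session after the first cycle of docetaxel (fourth chemotherapy), followed by a wash-out period of 6 days". The regimen (Participants / Recruitment) is "three cycles of 3-weekly epirubicin followed by three cyles of 3-weekly docetaxel", so on the stated timing both sessions probably fall within one docetaxel cycle, at different distances from the dose.
- **Model.** Sample size and analytical plan: "Using a generalized estimating equations framework for continuous outcomes to determine time (baseline, pre-, post, 24- and 72 h", continuing "and intervention (low-/ heavy-load) effects, the interaction between time and intervention will be considered". The levels listed for time are assessment points around a session. Neither session number nor sequence is named here or elsewhere in the article.
- **Possible source of a shift.** Discussion: "generalized edema characterized by an increase in the size of the interstitial compartment of extracellular fluid is a potential side effect to taxane-based chemotherapy". The authors add that such fluid, together with impaired lymph transport, might contribute to swelling of the at-risk arm, and that exercise might hypothetically counter it.
- **Reference value.** The sample size rests on change from baseline to 72 h, while the model lists baseline and pre-exercise as two separate time levels. The article does not say which of them is the reference for change.

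**The concern.** In a two-period cross-over, anything that differs between the first and second session, whatever the load, enters each woman's heavy-minus-low difference. It enters with a plus sign if heavy came second and a minus sign if heavy came first. A period term removes it. Without one, it stays in the residual spread of the differences, and it also moves the estimate when the two sequences end with unequal numbers.

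Here the primary outcome is arm extracellular fluid, and the authors themselves name a drug-related source of extracellular fluid acting around the time of both sessions. At stake is part of the precision for which the Discussion chooses a cross-over, and a limited bias if withdrawals or the allocation list leave the sequences unequal.

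**Working it through.** **Inputs.** SD 1.9, margin 3, 90% power, two-sided 90% interval, 18 patients raised to 20 (Sample size and analytical plan); 1:1 allocation to order (Concealed randomization). Let P be the mean session-2 minus session-1 shift in the analysed quantity, the same for both loads. The article gives no value; 0 to 3 L-Dex units is an assumption.

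**1. The plan's own figure.** n per group = 2 × (SD × (z0.95 + z0.95) / margin)² = 2 × (1.9 × 3.290 / 3)² = 8.68, so 9 per group and 18 in total. The stated 18 is reproduced, by a parallel-group equivalence formula that involves neither pairing nor period. The article does not say whether 1.9 is the SD of the within-participant difference or of the change in one session, so both cases are carried: SDd = 1.9, or SDd = 1.9 × √2 = 2.69 (uncorrelated sessions).

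**2. Where a shift would enter.**
- Change from the same-session pre-exercise value: a pure shift in level between weeks drops out. Only a different course over the two 72 h windows remains.
- Change from a single earlier baseline, if that is what baseline means: a level shift stays in.
- The intervention main effect: this compares levels, so a level shift stays in.
- L-Dex is derived from the impedance ratio of the two arms, so generalised fluid cancels in part, but fluid retained in the at-risk arm does not.

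**3. Precision, balanced sequences.** The plain within-participant difference stands in for the GEE load contrast. Its SD without a period term is √(SDd² + P²), so the interval widens by the factor √(SDd² + P²) / SDd:

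| P (assumed) | SDd = 2.69 | SDd = 1.90 |
|---|---|---|
| 0 | 1.00 | 1.00 |
| 1 | 1.07 | 1.13 |
| 2 | 1.25 | 1.45 |
| 3 | 1.50 | 1.87 |

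Simulation (100,000 trials per setting) agrees. At 10:10 and P = 2, the 90% half-width without versus with a period term is 1.29 versus 1.03 (SDd 2.69) and 1.07 versus 0.73 (SDd 1.90), ratios of 1.25 and 1.47. The second is slightly above 1.45 because the sample variance divides by n − 1.

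**4. Bias, unequal sequences.** Bias = P × (n1 − n2) / (n1 + n2).
- 9:9 or 10:10: 0.
- 10:8: P × 2/18 = 0.11P, or 0.22 units at P = 2.
- 11:7: P × 4/18 = 0.22P, or 0.44 units at P = 2.

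The period-adjusted estimate was unbiased in every simulated setting.

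**5. Against the 3-unit margin.** With no true load difference, the simulated probability that the 90% interval excludes ±3 stays at 0.96 or more without a period term for P up to 2, in all splits and both SDs. The worst setting (11:7, P = 3, SDd 2.69) gives 0.85 without the term and 0.99 with it.

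**6. Cost of the term when P = 0.** At 10:10 the mean standard error is the same with and without it (0.419 for SDd 1.90). At 11:7 it rises from 0.442 to 0.452 (SDd 1.90) or from 0.624 to 0.640 (SDd 2.69), about 2–3%.

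**The case against.** A reader might infer that the protocol itself predicts a shift between the sessions. It does not. The Discussion speaks of edema as a potential side effect that might contribute to arm swelling, and nowhere compares session 1 with session 2. The text supports plausible, not likely.

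Other points on the plan's side:

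- *Each session has its own pre-exercise measurement, and L-Dex is a between-arm ratio.* This stands for change from the same-session value. It does not cover the intervention main effect or a change from a single earlier baseline, and the article leaves open which reference is used.
- *1:1 allocation balances a period effect.* It does, if completers are balanced. The article states no blocking, though it may simply omit it. If the list is unblocked (an assumption), a 12:8 or worse split of 20 has probability 0.503. The Safety section also withdraws women with persisting signs, which could unbalance the sequences further.
- *A wider interval is the cautious error when the aim is to exclude 3 units.* This is true for that criterion. It does not hold for the planned two-tailed tests at 0.05: there, lost precision makes a non-significant result more likely, in a trial whose hypothesis is no difference.
- *The article condenses a fuller plan, and period is a nuisance term that it might leave out.* This stands as a caveat: the full plan may contain it. The article does, however, name the effects of its model, and the set it names is incomplete for this design.

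**Conclusion.** The point holds as an improvement to the stated model. The article names time, load and their interaction but no period term, in a two-period cross-over where a period effect is plausible. With balanced sequences the omission costs precision only: nothing at P = 0, 7–13% wider intervals at P = 1, 25–45% at P = 2. With unequal completers there is also bias, 0.22P at 11:7, or 0.44 units at P = 2 against a margin of 3.

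The documents do not support a claim that the primary comparison is invalid or that its conclusion would probably change, since the chance of meeting the margin criterion stays at 0.96 or more for P up to 2. These figures rest on the assumed P, on the two readings of the SD of 1.9, and on the simple paired difference as a stand-in for the GEE contrast.

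**What to change.** Add period (session 1 or 2) and period-by-time as fixed effects to the primary GEE. Estimate heavy minus low within participant as change from the same-session pre-exercise value, and say what the separate baseline level is used for. A sequence term is optional; the within-participant load contrast does not need it. If the full analysis plan already contains the period term, aligning the article's description with it is enough.

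The cost is a sentence or two of text, about one degree of freedom per contrast, and a few extra parameters in a model with about 20 clusters. When there is no period effect, essentially no precision is lost with balanced sequences, and about 2–3% of the standard error at 11:7.
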